## Abstract

**Background:**

Nutrition education programs in schools have been effective in improving children’s knowledge and behaviours related to food and nutrition. However, teachers find it challenging to implement such programs due to overcrowded curricula. Integrating nutrition with core subjects such as mathematics could potentially address time constraints and improve the learning of both. The primary aim of this randomized controlled trial (RCT) is to evaluate the impact of a cross-curricular nutrition and mathematics program on primary school students’ portion size estimation skills. Secondary aims include impact on their nutrition knowledge, attitudes towards mathematics and evaluating the quality of the lessons.

**Methods:**

Twelve Year 3–4 classes from Catholic schools in New South Wales, Australia will be randomised to intervention (*n* = 6) or control (*n =* 6) groups. Teachers in the intervention group will receive a professional development workshop and resources to teach 4–5 lessons on portion size and measurements across 1–4 weeks. Outcome measures include portion size estimation skills, nutrition knowledge and attitudes towards mathematics, with data collected during three school visits (pre-intervention, immediately post-intervention, 4 weeks post-intervention). Additionally, teaching quality will be assessed in both intervention and control groups and process evaluation undertaken using teacher interviews and student focus groups.

**Discussion:**

This RCT uses an innovative approach to improve both nutrition and mathematics related learning outcomes among primary school children. It has the potential to impact teaching practices regarding integration of nutrition into curricula and enhance the implementation of nutrition education interventions.

**Trial registration:**

Australian and New Zealand Clinical Trials Register ACTRN12619001071112 31/07/2019.

## Background

Healthy eating patterns promote optimal growth and development throughout infancy and childhood [1]. A healthy diet has benefits for overall well-being, with some studies reporting better school performance [2–4]. Dietary behaviour trends over recent decades show an increase in snacking frequency [5, 6], consumption of sugar-sweetened drinks [7] and larger portion sizes [8] while fruit and vegetable intake have decreased [5]. The latest National Health Survey (2017–18, Australia) recently reported that only 6.6% of New South Wales’ (NSW) children aged 2–17 years met recommendations for daily serves of both fruit and vegetables [9]. Furthermore, almost one-third (30.8%) consumed sugar sweetened drinks on 1–3 days per week. Establishing healthy eating habits during childhood is important as these behaviours tend to track into adulthood [10, 11].

Research indicates that it is not only a matter of what we eat, but also that the amount we consume plays a key role in nutrition-related health [8, 12, 13]. With food portions offered often being supersized, individuals are more likely to consume more food and drinks [14], which increases energy intake [15–17]. Both children and adults perceive serve size recommendations and portion size estimation as confusing [18–21]. Additionally, many people of all ages have difficulties estimating food volumes and portion sizes accurately with multiple studies showing that consumers’ estimations deviate largely from standard serve sizes [19, 22–24]. This might partly explain why large portions offered can lead to an increased consumption, with individuals not stopping once they consume ‘recommended’ amounts of food. Portion size education and training improve individual’s portion size estimation and knowledge [25–27]. Research shows that using (visual) estimation aids can be effective in reducing portion size estimation errors [28–31]. However, the effectiveness of such educational programs and portion size estimation aids in children and adolescents remains unclear [20]. Interventions on portion size education that target this specific population age group are therefore needed.

Schools are an ideal environment to provide nutrition or portion size education. A large number of children can be reached as they are in class during the majority of the week and for a prolonged period of their childhood [32, 33]. Theoretically, teachers have the potential to influence children’s dietary behaviour and knowledge through nutrition education [32, 34]. In practice, teachers experience several barriers to teaching nutrition in the classroom. Barriers such as lack of time and competing demands have been reported frequently [35–43]. Resources are often scarce and education materials are not ‘ready to go’ or not linked to curricular learning outcomes [35, 37, 41, 44]. As a result, difficulties arise when trying to teach nutrition as a sole subject [45] and the teaching of core curricular subjects is prioritised [33, 35, 38, 40]. This highlights the needs for school-based nutrition interventions that involve strategies to eliminate these time-related barriers.

An integrative or cross-curricular approach has been recommended to combat these time constraints faced by teachers [35, 41, 44, 46]. Embedding nutrition into core academic subjects such as Mathematics, English or Science would minimally affect the time spent on these subjects [37, 44, 45, 47]. Subsequently, teachers might be better able to integrate nutrition education programs within existing lessons and be more likely to implement these [44]. Another advantage of integrating nutrition with existing subjects is that it might enhance learning by creating real-life contexts relevant to the students [46–49]. Dudley et al. found that cross-curricular strategies have a positive effect on nutrition knowledge and dietary behaviours amongst schoolchildren [33]. Furthermore, findings from the FoodMASTER initiative, a hands-on mathematics and science curriculum that uses nutrition and food concepts as tools for teaching primary school children, show that a food-based science curriculum improves students’ nutrition [50], mathematics [49] and science knowledge [51].

Similar strategies could be used to integrate portion size education into the primary school curriculum. To accurately estimate portion size, individuals use essential skills including comparison of different amounts of food to other foods, or standard measurement units or estimation aids [52]. Such skills require understanding of basic mathematical concepts [53, 54] including volume and capacity [55]. The link between nutrition and mathematical concepts has been discussed, highlighting that it may be beneficial for development of skills related to both subject areas [48, 53–57]. A recent paper explored teaching practices related to the integration of nutrition and mathematical concepts among Australian primary school teachers. Although teachers reported using nutrition-related examples for their mathematics teaching, the integration of nutrition and mathematics could be substantially improved [55].

To the best of our knowledge, no previous interventions have reported the impact of a classroom-based nutrition education program focussing on portion size estimation nor the integration with mathematics in schools. A newly developed teaching unit incorporates the factors discussed above to maximize its effectiveness in relation to educational outcomes and to optimize implementation in the classroom. This cluster randomised controlled trial (RCT) will investigate the efficacy of a teaching unit integrating nutrition and mathematics in primary school children (CUPS: Cross-curricular Unit on Portion Size).

## Methods/design

### Aim and hypotheses

The overall aim of this RCT is to determine the effect of integrating nutrition into mathematics lessons on primary school children’s portion size estimation skills, nutrition knowledge and attitudes towards mathematics, and to explore teaching quality of the CUPS program.

The research questions for this study are:
What is the impact of the CUPS intervention on primary school students’ portion size estimation skills?What is the impact of the CUPS intervention on primary school students’ nutrition knowledge and attitudes towards mathematics?What is the impact of the CUPS intervention on the teaching quality?Is the CUPS intervention feasible for Stage 2 teaching?

It is hypothesized that the CUPS intervention group will show improvements in all outcome measures in comparison to the control group.

### Study setting and design

The CUPS intervention program is a RCT evaluating intervention effectiveness in a primary school setting. Ethics approval has been obtained from the University of Newcastle and the Catholic Diocese of Newcastle-Maitland in NSW, Australia. The CUPS trial is registered with the Australian and New Zealand Clinical Trials Registry (ACTRN12619001071112). The “Standard Protocol Items: Recommendation for Interventional Trials” (SPIRIT) was used to guide design, conduct and reporting of this study (see Additional file 1) [58].

### Recruitment and study participants

The CUPS trial will be conducted in primary schools from the Newcastle and Hunter region of NSW, Australia. Twelve schools from the Catholic Diocese of Newcastle-Maitland will be recruited to participate. From each school, one Stage 2 class (Year 3 and/or 4) will be invited. Students in Stage 2 will be selected as volume and capacity are introduced in this Stage in the NSW K-10 Mathematics syllabus [59]. All 44 Catholic primary schools within the Newcastle-Maitland region will be contacted to invite them into the study. If greater than twelve schools respond to participate, schools will be randomly selected. Principals, teachers, parents and students will need to provide their written informed consent. An email will be sent to the school principals containing Information Statements and Consent Forms. Principals will be followed up by either a reminder email or phone call. Upon receipt of the Principal’s consent, teachers’ Information Statements and informed Consent Forms will be provided to the school to distribute to all Year 3 and/or 4 teachers. To avoid teachers feeling pressured to participate, schools will be asked to send the information through email listings via an administrative staff member. A member of the research team will contact the teachers to organise a school visit and provide students with information about the study. All students wanting to participate in this study will be required to return a Consent Form, which has been signed by the students and their parents/guardians. Signed forms will be returned to the research team via a collection point at the school’s office. All Consent Forms collected through the school’s office will be kept confidential and individual’s privacy will remain protected.

Class groups in which the teacher has already taught all nutrition and volume capacity content covered in the planned intervention will be excluded. In addition, teachers with formal nutrition training/professional certification in nutrition or dietetics will be ineligible. All students of consenting teachers will participate in the CUPS program as part of their normal classroom activities. However, only data from students who return their consent letters will be used in analyses. Enrolment of the teachers and their students will be performed by a member of the research team. Figure 1 summarises the participant recruitment and group allocation flowchart.

**Fig. 1 Fig1:**
[figure not shown]
CUPS intervention design including recruitment, group allocation, intervention outline and measurements

After baseline measurements, schools will be randomly allocated to either the intervention or wait-list control groups. Participating schools will be matched based on size and socio-economic demographics using the index of community socio-educational advantage (ICSEA). This index produces scores that take into account family background information provided by the families to the schools and includes parental occupation and (non-)school education levels achieved. An independent researcher who is not involved in the CUPS program will use a simple computerised sequence generation to perform the randomisation of the matched schools. Following the randomisation of the schools, a member of the research team will assign the participating schools to either the intervention or the control condition.

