### Sample size calculation

A power calculation was conducted to determine the sample size necessary to detect changes in the primary outcome of portion size estimation (% deviance from actual). Based on proportional error reported when using an international food unit [29], detection of a 5% reduction in error was regarded as clinically important. A sample size of 84 was needed to detect a 5% reduction in portion size estimation error (from 20 to 15%) assuming an alpha of 0.05 and power of 80%. To adjust for clustering, the following correction factor was applied [1+ (m – 1) x ICC] [60], where m = students per school and ICC = the intra-class correlation coefficient (between school variance / (between school variance + within school variance). Assumptions are based on clustering at the school level (one class recruited per school, with 25 students per class), and an ICC of 0.1 based on data from a large scale study in Australian schools [61], resulting in a correction factor of 3.4. The resulting student sample is 285 students at 12 schools for a minimum detectable effect size of d = 0.62.

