### Statistical methods

This intervention is designed to obtain both qualitative and quantitative data. The Statistical Package for the Social Sciences (SPSS) 24 will be used for the data analyses of the primary and secondary outcomes. Descriptive statistics will be explored for all variables including mean, median, standard deviation, and percentages (as data type requires). Differences of means and 95% confidence intervals (CI’s) of quantitative outcomes will be determined using linear mixed models. These models will assess the impact of treatment group (CUPS vs control), time (baseline, follow-up 1 and follow-up 2) and the group-by-time interaction as fixed effects. Covariates in this model will include gender and year level (Year 3 or Year 4). The base model will be further specified by taking clustering of students within classes into account. An alpha level of *p* < 0.05 will be used as cut-off for statistical significance.

Qualitative data from the interviews and focus groups will be transcribed and analysed using a thematic approach. The computer program Leximancer will be used to perform qualitative analyses in a standardised general inductive manner. Leximancer uses automatic content analysis software to visually represent the main concepts from the interviews and focus groups, and to display how these concepts are related [73]. Smith and Humphreys (2006) validated Leximancer using previously published comprehensive evaluation criteria [74]. First, labels or codes derived from the qualitative data will be formulated. Subsequently, these codes will continually be revised and expanded following the coding of additional transcripts. Arising themes will be identified and defined once all transcripts have been coded.

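### Schools are matched on size and ICSEA before randomisation, but the stated model adjusts only for gender and year level, so the analysis does not reflect the allocation

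*Protocol article*

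**What the plan says.** Under Recruitment and study participants (the text after the Fig. 1 legend), the article states: "Participating schools will be matched based on size and socio-economic demographics using the index of community socio-educational advantage (ICSEA"). An independent researcher will then "use a simple computerised sequence generation to perform the randomisation of the matched schools". The article does not describe the form of the matched sets or say in words that allocation is made within them.

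Under Statistical methods, the linear mixed model has group, "time (baseline, follow-up 1 and follow-up 2) and the group-by-time interaction as fixed effects". It continues: "Covariates in this model will include gender and year level (Year 3 or Year 4"). Clustering enters as follows: "The base model will be further specified by taking clustering of students within classes into account". One class is recruited per school, so class and school are the same unit. School size, ICSEA and matched set are not among the terms named.

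The Sample size calculation uses 25 students per class and an ICC of 0.1, and makes no allowance for matching.

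**The concern.** Variables used to restrict allocation normally belong in the analysis. If size and ICSEA are prognostic, matching on them reduces the true sampling variance of the arm difference. A model without them leaves the differences they explain in the estimated between-class variance, so the reported standard error describes an unmatched design. The result would be intervals wider than they need be and a test below its nominal level, in a trial with only 12 randomised units. The trial holds both variables already, since it needs them to match.

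**Working it through.** **Inputs from the article.** 12 classes, 6 per arm; 25 students per class; ICC 0.1; a fall in error from 20 to 15%; alpha 0.05 (taken as two-sided); power 80%; 84 students before and 285 after the clustering correction; d = 0.62.

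**Assumptions.** The share R² of between-school variance explained by size and ICSEA is not given, so it is varied. The matched sets are taken as six pairs, split between arms.

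**The plan's own figures.** With 42 per arm, the detectable d at 80% power is 0.611 (normal) or 0.619 (t-based), against 0.62 stated. The design effect is 1 + 24 × 0.1 = 3.4, and 84 × 3.4 = 285.6, against 285 stated. Both reproduce. The implied SD is 5/0.62 = 8.06, and 285/12 = 23.75 students per class.

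**Between-arm contrast of school means at one visit** (SD units).

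- Variance of a school mean without the factors: V = 0.1 + 0.9/23.75 = 0.1379.
- Standard error: √(2V/6) = 0.214, or 1.73 percentage points.
- With the factors: V = 0.1(1 − R²) + 0.0379.
- Two school-level covariates leave 8 df (critical t 2.31, against 2.23 on 10 df). The adjusted column assumes they capture the whole share and are balanced between arms.
- The unadjusted columns come from simulation, and the adjusted power from the noncentral t.

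| Assumed R² | Reported SE / true SE | Type I error, unadjusted | Power, unadjusted | Power, two covariates (8 df) |
|---|---|---|---|---|
| 0 | 1.00 | 5% | 74% | 72% |
| 0.3 | 1.13 | 3% | 76% | 82% |
| 0.5 | 1.25 | 2% | 78% | 89% |
| 0.7 | 1.43 | 1% | 80% | 95% |

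At R² = 0.1 the two analyses are level at about 75%. Six fixed pair effects would leave 5 df (critical t 2.57) and give 64, 74, 82 and 90% on the four rows, below the two covariates throughout.

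**Group-by-time contrast (change from baseline to one follow-up).** This takes 24 per class and total variance 8.06² = 65.0, and assumes half of the within-school variance lies between students. The residual variance is then 0.45 × 65.0 = 29.3. A stable school effect cancels from the change, so the standard error is √(4 × 29.3/144) = 0.902. It is the same with and without matched-set terms at R² of 0, 0.5 and 0.9.

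**Group-by-time when classes also differ in change.** Let class-by-time variance be an assumed 5% of the total (3.25), with residual variance 0.40 × 65.0 = 26.0. The true standard error is √(4 × 3.25(1 − f)/6 + 4 × 26.0/144), where f is the share of class-by-time variance explained by the matching. It equals 1.70, 1.34 and 0.97 for f = 0, 0.5 and 0.9.

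- A model that allows for class-by-time variation but omits the factors would report about 1.70 in each case, which is too wide when f > 0.
- A model with only a class intercept would report about 0.885 (approximate), which is too small in each case.

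**The case against.** A reader might infer that the reported standard errors are certainly too wide and that the gain from matching is lost. The documents do not support that. Nothing in the article says how strongly size or ICSEA relates to portion size error, and at R² = 0 there is no inflation. The listed model includes group-by-time, where a stable school effect cancels. In that case main-effect covariates would leave the test unchanged. If classes differ in change and only a class intercept is fitted, the error runs the other way. Nor is the gain lost: matching still gives balance and a smaller true variance, and unadjusted power rises from 74 to 80% across the table. What is missing is credit for it in the reported standard error.

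A reader might also take "simple computerised sequence generation to perform the randomisation of the matched schools" to mean an unrestricted draw that discards the matching. The more natural reading is that allocation uses the matching, with the adjective describing how the sequence is generated. The wording is ambiguous but not shown to be wrong.

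Finally, this is a condensed article, and its covariate wording need not be exhaustive. That tempers the point but does not remove it. The article does name its covariates, and neither is a factor used in the allocation.

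**Conclusion.** The mismatch stands: allocation uses size and ICSEA, and the stated model names neither. Its consequence is conditional.

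- **Between-arm contrast at follow-up.** If the two factors explain 30 to 70% of between-school variance, the unadjusted test runs at about 3 to 1% instead of 5%. It also gives up about 5 to 15 points of power (76 v 82%, 80 v 95%).
- **Group-by-time.** Precision goes uncredited only if the factors predict change. With stable school effects nothing is inflated.

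These figures rest on assumed variance shares, six assumed pairs and the article's ICC of 0.1. Where it arises through an unadjusted between-arm contrast, the error is conservative, so it does not threaten a positive finding. It is a worthwhile improvement that costs little to make before analysis.

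**What to change.** Add ICSEA and school size as continuous school-level covariates to the student-outcome models. Where the test is group-by-time, include their interactions with time and allow for class-level variation in change, because main effects alone would not alter that test. Base inference on school-level degrees of freedom, and do not use six fixed pair effects. State the form of the matched sets and that allocation is made within them.

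The change is one of wording, using data the trial already needs for matching. It costs about two school-level degrees of freedom (10 to 8). That is roughly 2 points of power (74.1 to 71.7%) if the factors are not prognostic, with a gain once they explain more than about 10% of between-school variance.

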#### Portion size estimation skills

The primary outcome will be students’ portions size estimation skills which will be assessed by determining the ability of a student to estimate the correct portion size of a given food. Mathematics cubes will be used by the children to measure food volume of a set of food models [64]. Researchers will briefly explain the task to the children after which they are asked to perform this themselves. They will be given a variety of food models including an apple, chicken filet pieces, broccoli/cauliflower flowerets, feta cubes and penne pasta. Students will have to compare the volume of both cubes and food models to estimate the number of cubes that correspond with the portion size. The correct food volume expressed as number of cubes will be compared with student answers to determine their ability to estimate portion sizes as percentage deviance from the actual. This methodology has been used in previous research to explore individuals’ portion size estimation skills [29, 65]. Children will also be asked to report the food volume using other units of measurement (e.g. how many serves based on the AGHE). This outcome variable will be taken at all three school visits (baseline, follow-up 1 and follow-up 2).

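### Schools are allocated after baseline but matched only on size and ICSEA, so the class's baseline portion size error is left unused: a modest, cheaply avoidable loss with 12 clusters

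*Protocol article*

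**What the plan says.** The allocation paragraph, which follows Fig. 1 under Recruitment and study participants, sets the order of events: "After baseline measurements, schools will be randomly allocated to either the intervention or wait-list control groups". It then names the matching variables: "Participating schools will be matched based on size and socio-economic demographics using the index of community socio-educational advantage (ICSEA"). An independent researcher randomises the matched schools. The paragraph does not say whether the matched sets are pairs, and baseline portion size error is not among the matching variables.

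Under Portion size estimation skills, the primary outcome is the percentage deviance on the cube task, and "This outcome variable will be taken at all three school visits (baseline, follow-up 1 and follow-up 2"). The Abstract gives six classes per arm.

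Statistical methods specifies a linear mixed model with group, time (baseline and both follow-ups) and their interaction. Its covariates are gender and year level, and it accounts for pupils clustered within classes. Baseline therefore enters as an outcome row, not as a covariate.

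**The concern.** With 12 schools, randomisation alone balances the arms only loosely, so the choice of matching variables matters more than in a large trial. Matching helps to the extent that the variables predict the outcome. ICSEA may well do so. School size is at best an indirect marker of one class's skill at estimating food volume. The class's own baseline score on the same task is the closest predictor to hand, and the plan collects it before allocation.

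Two things are at stake. One is some precision in a trial with few clusters. The other is how convincing the result looks if the arms visibly differ at baseline on the primary outcome. The matching rule is fixed by the protocol and acts at allocation, so a later analysis plan can recover only part of what is lost.

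**Working it through.** **Inputs.** From Sample size calculation: a 5-point target (20% to 15% error), d = 0.62, 285 pupils, 12 schools, 25 pupils per class and ICC 0.1. From the Abstract: six schools per arm. The SD is not stated and is derived here. The test is taken as two-sided because that reproduces the plan's figure.

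**Step 1: reproduce the plan's figure.** The implied SD is 5/0.62 = 8.06 points. A two-sided t-test at alpha 0.05 and 80% power for d = 0.62 needs 41.8 per arm, so 42 per arm and 84 in total, as stated. The design effect is 1 + (25 − 1) × 0.1 = 3.4, and 84 × 3.4 = 285.6, stated as 285. The inputs hang together.

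**Step 2: chance baseline gap between arms.**
- Total variance: 8.0645² = 65.04.
- Between-class variance: 0.1 × 65.04 = 6.50. Within-class variance: 58.53.
- Pupils per class: 285/12 = 23.75.
- Variance of a class mean: 6.50 + 58.53/23.75 = 6.50 + 2.46 = 8.97.
- SD of the arm difference: √(2/6 × 8.97) = 1.73 points.
- Mean absolute gap: 1.73 × √(2/π) = 1.38. 95% range: ±1.96 × 1.73 = ±3.4.

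This gives no credit to size and ICSEA. If they explain a share R² of the between-school variance (an assumption; the document gives no figure), the SD becomes √(2/6 × [6.50(1 − R²) + 2.46]).

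| R² of size and ICSEA | SD of gap | P(gap ≥ 2.5) |
|---|---|---|
| 0 | 1.73 | 15% |
| 0.3 | 1.53 | 10% |
| 0.5 | 1.38 | 7% |

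The formula treats matching as perfect. In simulation, pairs are not exact, and R² = 0.3 gives an SD of about 1.55 and a probability of about 11%. Hence the range of 7–11%.

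For sensitivity to the ICC with no benefit from matching, the 95% limit runs from 2.7 points at ICC 0.05 to 4.4 points at ICC 0.20.

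**Step 3: the gap after matching on baseline error.** Twelve schools were simulated, paired on the observed class mean and randomised within pairs. The SD of the gap falls to about 0.58 points, with a 95% limit near 1.1. If ICSEA is kept as a second matching variable, the SD is about 0.6–0.9, depending on the weight given to each and on how well the sets are formed.

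**Step 4: effect on the treatment contrast.** The correlations over time are assumed (school level/pupil level). The comparison is pairing on baseline error against matching that is not prognostic, with contrasts computed on class means.

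| Correlations | SE of change contrast | Reduction | SE of baseline-adjusted contrast | Reduction |
|---|---|---|---|---|
| 0.6/0.4 | 1.651 → 1.469 | 11% | 1.533 → 1.454 | 5% |
| 0.8/0.5 | 1.298 → 1.214 | 6% | 1.276 → 1.209 | 5% |
| 0.9/0.6 | 1.042 → 1.002 | 4% | 1.053 → 1.001 | 5% |

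If ICSEA explains 30% of between-school variance, the comparator is the plan's own matching. The reductions are then about 4–9% for the change contrast (for example 1.626 → 1.478 at 0.6/0.4) and 4–5% after adjustment (for example 1.264 → 1.208 at 0.8/0.5).

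**Step 5: where the analysis must follow.** A class-mean baseline covariate added to the planned model is constant over time within a class. It shifts the class's level at every visit and leaves the group-by-time contrast alone. In a simulated dataset the estimate (−6.755) and its SE (1.310) were identical with and without it. Baseline has to move from the outcome side to the covariate side for the SE to reflect the better balance.

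**The case against.** Matching on size and ICSEA is a valid choice, and nothing in the protocol contradicts it. A chance gap is not bias, and the planned model measures the effect relative to baseline, so a starting difference is largely subtracted. All of this stands and limits the point to efficiency and credibility. The subtraction is not complete, however. A change contrast removes the whole baseline gap although class means regress toward the average, so part of a chance gap passes into the estimate unless the correlation over time is 1.

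The protocol also does not say when matching is done, or that all 12 classes are tested and scored before the first school is allocated. That is the natural reading of the sequence, but it is a reading, and the fix depends on making it explicit.

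A reader might infer two stronger things:

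- **That the arms are likely to start several points apart.** The plan's figures do not support this. The mean gap is about 1.4 points, a gap above 3 points has probability 8%, and one above 5 points 0.4%, even with no credit for the existing matching.
- **That the main benefit of randomising after baseline is thrown away.** It is not. In a cluster trial that benefit is that baseline testing, and any consent obtained by then, cannot be influenced by known allocation. The plan keeps it.

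**Conclusion.** The point holds as a moderate design weakness. The stated rule leaves out the most direct predictor that will be available at allocation. The expected gain from using it is about 4–11% in the SE of the change contrast and about 5% or less after baseline adjustment, together with near-elimination of baseline gaps as large as half the target effect. Larger claims of gain would need weak correlation over time, an unadjusted change score and a comparator with no useful matching at all.

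The figures rest on an SD derived from d = 0.62, on the ICC of 0.1 holding at baseline, on assumed correlations over time, and on an unknown prognostic value of size and ICSEA. The more prognostic those two are, the smaller the gain. It should be changed if allocation has not yet taken place, and it does not threaten the validity of the trial.

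**What to change.** 1. **Allocation paragraph (Recruitment and study participants).** State that schools are matched on class mean baseline portion size error together with ICSEA, with school size only as a tie-breaker. State that matching is done once all baseline cube tasks are scored, and that the independent researcher then randomises within the matched sets.
2. **Statistical methods.** Estimate the effect at follow-up 1 and follow-up 2 from a mixed model with follow-up scores only as outcomes and baseline portion size error as a covariate, keeping the class clustering, gender and year level. Do not simply add a class-mean covariate to the model that has baseline as an outcome row.

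**Cost.** All 12 classes must be tested and scored before any school is allocated. Schools visited early would wait for the last one, and the teacher workshop comes after allocation. The delay has to be reconciled with the Outcomes section, which places follow-up 1 at 1–4 weeks after the baseline visit. Matching on school size becomes slightly looser. No pupils, visits or measures are added.
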